### Measurement of outcomes

#### Primary outcome

The primary outcome is the live birth rate after 20 weeks of gestation following the fresh transfer.

#### Secondary outcomes

Secondary outcomes include pregnancy outcomes, maternal safety and obstetric and perinatal complications. Detailed information is provided in Table 2. Maternal safety is an important part of the secondary outcomes. The incidence of OHSS is the key indicator of maternal safety and is classified as mild, moderate or severe according to the RCOG guideline [22, 23]

**Table 2 Tab2:** Secondary outcomes and related definition

Secondary outcomes	Definition
Clinical and laboratory outcomes	
Total amount of FSH	Total amount of FSH used for ovarian stimulation
Number of follicles > 12 mm	The number of follicles > 12 mm measured by transvaginal ultrasound on the day of the trigger or the day before
Number of oocytes obtained	Number of oocytes obtained during oocyte retrieval
Number of embryos obtained	Number and quality of embryos obtained
Proportion of good-quality embryos	Embryos with 4 cells and < 25% fragmentation on day 2 or with ≥6 cells and ≤ 10% fragmentation on day 3, the proportion of oocytes resulting in top quality day 2 (or day 3) embryos according to validated morphological criteria
Oocyte fertilisation rate	The number of zygotes with 2PN over the number of mature oocytes for ICSI or over the number of oocytes for conventional insemination
Endometrial thickness	Endometrial thickness measured by transvaginal ultrasound on the day of the trigger or the day before
Serum E2 level	Serum E2 level on the day of the trigger or the day before
Serum P level	Serum P level on the day of the trigger or the day before
Serum testosterone level	Serum testosterone level on the day of the trigger or the day before
Follicular fluid E2 level	E2 level in the follicular fluid
Follicular fluid testosterone level	Testosterone level in the follicular fluid
Follicular fluid inhibin B level	Inhibin B level in the follicular fluid
Follicular fluid AMH level	AMH level in the follicular fluid
Pregnancy outcomes	
Miscarriage	Spontaneous loss of an intrauterine pregnancy before 20 completed weeks of gestational age
Clinical pregnancy	Presence of one or more intrauterine gestational sacs at 6 weeks of gestation
Ongoing pregnancy	Presence of one or more gestational sacs and foetal heartbeat after 12 weeks of gestation
Maternal safety outcomes	
OHSS	It is classified as mild, moderate or severe according to the degree of abdominal distention, ovarian enlargement and respiratory haemodynamic, and metabolic complications. Diagnosed by ultrasound, blood testing and physical examination according to the RCOG Guideline
Ectopic pregnancy	A pregnancy outside the uterine cavity, diagnosed by ultrasound, surgical visualisation or histopathology
Obstetric and perinatal complications	
Hypertensive disorders of pregnancy	Including pregnancy-induced hypertension, preeclampsia and eclampsia
Antepartum haemorrhage	Including placenta previa, placenta accreta and unexplained
Multiple pregnancies	Pregnancy with more than one foetus
Birth weight	Including low birth weight (weight < 2500 g at birth), very low birth weight (< 1500 g at birth), high birth weight (> 4000 g at birth) and very high birth weight (> 4500 g at birth)
Small for gestational age	Birth weight less than the 10th centile for the sex-specific birth weight for a given gestational age reference
Preterm delivery	Birth of a foetus delivered after 28 and before 37 completed weeks of gestational age
Congenital anomaly	Structural or functional disorders that occur during intrauterine life and can be identified prenatally, at birth or later in life, including trisomy 21 syndrome, neural tube defect, congenital heart disease, cleft lip, excessive numbers of fingers or toes and hydrocephalus
Perinatal mortality	Foetal or neonatal death occurring during late pregnancy (at 28 completed weeks of gestational age and later), during childbirth, or up to seven completed days after birth

### Safety reporting

Adverse events (AE) are defined as any undesirable experience occurring to a subject during the trial. A serious adverse event (SAE) is any untoward medical event that results in death, is life-threatening (at the time of the event), requires hospitalisation or prolongation of existing inpatients’ hospitalisation, results in persistent or significant disability or incapacity, is a congenital anomaly or birth defect and is a new event of the trial likely to affect the safety of the subjects, such as an unexpected outcome of an adverse reaction.

SAE in this study includes moderate/severe OHSS, intraperitoneal haemorrhage or ovarian torsion after oocyte retrieval, ectopic pregnancy, severe preeclampsia, pregnancy complications leading to hospitalisation, stillbirth, birth defects and other serious medical events judged by researchers to meet the criteria of SAE.

### Statistical analysis

#### Sample size calculation

The primary hypothesis of this trial is that the letrozole group will increase the live birth rate when compared with the control group. This treatment will be considered effective if the proportion of women having a live birth is increased by 10% in absolute terms. With an 80% power and a one-sided 2.5% level of statistical significance, we will need to recruit 752 women (376 in each arm) to show an absolute difference of 10% from 35 to 45% between control and letrozole groups. Taking consideration of the dropout rate as 20% (such as cancellation of fresh embryo transfer because of high risk of OHSS), each group will include 450 women (a total of 900 women).

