### Study setting

This is an open-label randomised controlled superiority trial being performed in the Department of Obstetrics & Gynaecology, The University of Hong Kong, and the Centre for Reproductive Medicine, Department of Obstetrics and Gynecology, Peking University Third Hospital. Written informed consent was obtained from all participants before participation in the study.

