### Statistical analysis

The result will be analysed according to the intention-to-treat (ITT) principle. Per-protocol (PP) analysis will also be conducted as a sensitivity analysis. Baseline characteristics will be described by descriptive analysis and the balance among groups or subgroups will be assessed by analysis for different kinds of data. For continuous variables, the normality distribution will be estimated by using frequency histograms and the Kolmogorov-Smirnov test initially. If the continuous variables are normally distributed, they will be presented as means with standard deviations (SDs). If the continuous variables are non-normally distributed, their medians and interquartile ranges (IQRs) will be reported. For categorical variables, we will present the proportion between each group. In addition, the recruitment number, those participants lost to follow-up, protocol violations and other relevant data will also be reported. A comparison between groups will be performed using the independent sample *t*-test, Mann-Whitney *U* test for continuous variables or Pearson chi-square test/Fisher’s exact test for categorical variables as appropriate. The primary outcome will be compared using Pearson’s chi-square test or Fisher’s exact test as appropriate. Categorical secondary outcomes will be compared between two groups using a similar approach as the primary outcome. Student’s *t*-test or Wilcoxon test will be used as appropriate for continuous secondary outcomes, such as birth weight, etc. The relative risks (RR) and absolute rate differences (ARD) and their 95% confidence interval (CI) between the two groups will be calculated. And the 99% CI of the ARDs will be used to evaluate if the letrozole group is superior to the control group. Multiple variable logistic regression models will be used to assess the treatment effect adjusting for other potential confounding variables that are unbalanced in the baseline.

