Missing data will be treated as missing at random and will be imputed using the last observation carried forward (LOCF) method. For the missing values, a sensitivity analysis will be done under the hypothesis of the worst and the best outcomes for each missing individual. Therefore, all secondary outcomes will be considered exploratory. All statistical analyses will be done using the statistical package SPSS (version 26.0, released 2019, IBM corp., Armonk, NY, USA). Statistical significance is defined as *p* < 0.05 with two-sided testing.

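### The 10-point design difference is worded as a success criterion, although the trial is sized and analysed as a test of zero difference

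*Protocol article*

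**What the plan says.** The protocol article's Sample size calculation section makes three statements in sequence.

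- The hypothesis is directional and has no margin: "The primary hypothesis of this trial is that the letrozole group will increase the live birth rate when compared with the control group".
- The next sentence says when the treatment will count as working: "This treatment will be considered effective if the proportion of women having a live birth is increased by 10% in absolute terms".
- The calculation then uses the same 10 points as the difference to detect: "With an 80% power and a one-sided 2.5% level of statistical significance, we will need to recruit 752 women", "to show an absolute difference of 10% from 35 to 45% between control and letrozole groups".

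The Statistical analysis section sets out how the result is to be judged: "The primary outcome will be compared using Pearson’s chi-square test or Fisher’s exact test as appropriate", and "Statistical significance is defined as *p* < 0.05 with two-sided testing". It also says that superiority of letrozole will be evaluated from a 99% confidence interval for the absolute rate difference. None of these refers to 10 points. Study setting describes the design: "This is an open-label randomised controlled superiority trial".

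**The concern.** The sentence on effectiveness is phrased as a condition for a conclusion, not as a planning assumption. It does not say whether the 10 points refer to the true effect, the point estimate or a confidence limit, and no other section reconciles it with the superiority criteria.

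An observed gain of 7 to 9 points is quite plausible. With such a result, the text could support a claim of superiority (significant against zero) or a claim that the treatment is not effective (short of 10 points). The trial is open-label, and the choice between the two could be made after the result is known.

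**Working it through.** **Inputs.** Control 35%, letrozole 45%, 80% power, one-sided 2.5%, 376 per arm before dropout and 450 per arm randomised, all from Sample size calculation. The primary test, the 99% interval and the two-sided 5% level come from Statistical analysis.

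**Step 1. Reproduce the stated sample size as a test of zero difference.** With pooled variance under the null and no continuity correction:

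n = [z(0.975)·√(2·p̄·(1−p̄)) + z(0.80)·√(p₁(1−p₁) + p₂(1−p₂))]² / d²

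Here p̄ = 0.40, so 2·0.40·0.60 = 0.480. Also 0.35·0.65 + 0.45·0.55 = 0.475, and d = 0.10.

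n = [1.960·0.6928 + 0.8416·0.6892]² / 0.01 = [1.3579 + 0.5800]² / 0.01 = 375.6, which rounds up to **376 per arm**.

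This matches the plan. Two-sided 5% gives the same number. One-sided 5% would give 296, and one-sided 0.5% (the level of a 99% interval) would give 560. In this calculation 10 points is the assumed true effect and the null is zero.

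**Step 2. What the sentence would do if applied to the observed difference.** Exact binomial enumeration over both arms at a true 35% versus 45%, all women analysed. The test is the pooled z form of the chi-square test, with letrozole better.

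| | 376 per arm | 450 per arm |
|---|---|---|
| P(observed difference ≥ 10 points) | 0.503 | 0.514 |
| Power, two-sided 5% test | 0.799 | 0.869 |
| P(significant at two-sided 5%, difference < 10 points) | 0.295 | 0.354 |
| P(superior at the 99% level, difference < 10 points) | 0.09 | 0.18 |

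In every enumerated outcome with a difference of at least 10 points, the two-sided 5% test was also significant. Hence 0.869 − 0.514 ≈ 0.354 at 450 per arm, allowing for rounding.

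**Step 3. The range of results caught between the two statements.** Smallest observed gain reaching each criterion with about 35% live births in the control arm:

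| | 376 per arm | 450 per arm |
|---|---|---|
| Two-sided 5% | 7.2 points | 6.4 points |
| 99% level | 9.3 points | 8.4 points |

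At 450 per arm the gap therefore runs from 6.4 to just under 10 points at two-sided 5%, and from 8.4 to just under 10 points at the 99% level.

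**Step 4. An example.** Take 35% versus 43% with 450 per arm: z = 0.08 / √(2·0.39·0.61/450) = 2.46. This exceeds 1.96 but not 2.576. It is superior at two-sided 5%, not superior by the 99% interval, and short of 10 points. It shows the gap at the 5% level only. Under the 99% interval the two statements would agree on this result.

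**The case against.** The best defence is context. The sentence stands in the sample size section, between a hypothesis with no margin and a calculation that uses the same 10 points as the difference to detect. It does not mention an observed difference. The Discussion describes the sample as adequate to show a 10-point absolute difference, which is the language of a detectable effect. The analysis section, where decision criteria belong, contains no 10-point rule. Step 1 points the same way. This defence largely stands: a target difference is the likelier meaning.

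A reader might infer something stronger: that the plan has a definite second decision rule, that the trial therefore has only about 51% power, and that it runs at a one-sided error rate of about 0.1% to 0.2% (0.0009 at 450 per arm, 0.0021 at 376, under a common rate of 35%). The documents do not support that. Those figures exist only if the sentence is taken as a rule on the point estimate, which the text never says. Any threshold set equal to the assumed true effect is met about half the time, so 51% says little about this trial in particular. Quoting the gap only as 6 to 10 points would also ignore the 99% interval, under which it is narrower.

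The defence does not remove the wording itself. It is literally a success criterion, nothing reconciles it with the analysis section, and settling the choice between a 95% and a 99% interval would leave it in place.

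**Conclusion.** The point holds as a minor wording fault: the design alternative has been written as a condition for success. There is no demonstrated loss of power, because on the likelier reading the sentence only names the difference the trial is sized to detect.

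What remains is an ambiguity that matters only if the observed gain falls in the gap. On the literal observed-difference reading, with 450 per arm and a true 35% versus 45%, that would happen in about 35% of trials against the two-sided 5% test and about 18% against the 99% interval. With 376 per arm the figures are about 30% and 9%. All of them assume that every woman is analysed, that the design rates hold in that analysis set, and that the chi-square form of the test is used.

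**What to change.** 1. Reword the sentence in Sample size calculation so that an absolute increase of 10 points is only the difference the trial is sized to detect.
2. State one superiority criterion: the intention-to-treat primary test at two-sided 5% (equivalently one-sided 2.5%), which is the level that yields 376 per arm. Bring the 99% interval sentence in Statistical analysis into line with it.
3. Report the absolute rate difference with its 95% confidence interval and discuss it against 10 points as a description of clinical size, not as a second pass/fail test.

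The cost is a few sentences of wording, fixed before database lock, with no extra participants or data. The one small loss is a stricter threshold for the claim, which the sample size never supported.

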## Discussion

Letrozole is usually used for ovulation induction in anovulatory women and ovarian stimulation and intrauterine insemination for treatment of unexplained infertility. It is now routinely used in women with breast cancer undergoing fertility treatment in order to prevent recurrent breast cancer as a result of supraphysiological estradiol level following ovarian stimulation [14]. Its use in poor responders and normal responders in IVF may reduce the total gonadotropin dose required for ovarian stimulation without increasing the pregnancy rate [24–26]. The hypothesis of the present study is that adding letrozole to gonadotropin in the ovarian stimulation protocol in high responder patients can improve the live birth rate of women with anticipated high ovarian response in IVF. The present study is the first randomised study which provides high-quality evidence about the efficacy of co-administration of letrozole in high ovarian responders and IVF cycles and may open new insights into the clinical management of this group of women.

The strengths of the present study include randomisation, a large adequate sample size to show a 10% absolute difference in the live birth rate between the intervention and control groups and the live birth rate as the primary outcome, which is the most important clinical outcome in fertility treatment studies. Most women prefer to choose embryo transfer in the fresh cycle instead of transfer in frozen cycles because of time constrain, economic reasons and psychological factors, so the use of letrozole during ovarian stimulation for IVF producing a good number of oocytes with physiological levels of estradiol may reduce the adverse impact on endometrial receptivity and increase the success rate of the IVF treatment. To increase the external validity of this trial, we did not limit embryo transfer to day 3 or day 5 only and the results of day 3 and day 5 transfer will be separately analysed. The timing of embryo transfer is unlikely to influence the results because of randomisation in the study.

The limitation is the lack of cumulative live birth rate of the stimulated IVF cycle.

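### The 20% dropout allowance is multiplied rather than divided (450 per arm, not 470), and it treats cancelled fresh transfers as losses although the analysis is by intention to treat

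*Protocol article*

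**What the plan says.** All references are to the protocol article.

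- **Sample size calculation.** The inputs are "With an 80% power", "a one-sided 2.5% level of statistical significance" and the aim "to show an absolute difference of 10% from 35 to 45% between control and letrozole groups". From these the article concludes "we will need to recruit 752 women (376 in each arm"). It then takes a "dropout rate as 20% (such as cancellation of fresh embryo transfer because of high risk of OHSS), each group will include 450 women", 900 in total.
- **Primary outcome.** Live birth beyond 20 weeks, following the fresh transfer.
- **Statistical analysis.** "The result will be analysed according to the intention-to-treat (ITT) principle", with per-protocol as a sensitivity analysis. Significance is p < 0.05 "with two-sided testing".
- **Interventions; Embryo transfer and luteal support.** All embryos are frozen, with no fresh transfer, on grounds that include OHSS risk (judged partly on serum estradiol and oocyte number), raised progesterone, endometrial polyps or cavity fluid.
- **Discussion.** Among the strengths is "a large adequate sample size to show a 10% absolute difference in the live birth rate".

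The article does not say whether 35% and 45% are rates per woman randomised or per fresh transfer. Nor does it say how a woman with a cancelled fresh transfer counts in the ITT analysis.

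**The concern.** There are two separate faults.

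The first is arithmetic. To keep 376 women after losing 20%, one divides by 0.8. Multiplying by 1.2 gives too few, so the planned number misses the article's own requirement at the article's own dropout rate.

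The second is a mismatch between sizing and analysis. The sample size section gives a cancelled fresh transfer as its example of dropout, as if such a woman left the analysis. Under ITT she does not leave. She also cannot have the primary event, because she had no fresh transfer. She therefore counts as a non-event and shrinks the difference between the arms. Inflating for dropout replaces lost women; it does not restore a diluted difference.

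At stake is how a null result is read. If the trial is described as adequate for a 10-point difference while the ITT contrast is smaller, a non-significant result may be taken to rule out more than it does.

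**Working it through.** **Inputs.** From the sample size section: control 35%, letrozole 45%, power 80%, one-sided 2.5% (the same critical value as two-sided 5%, z = 1.960), loss 20%, final size 450 per arm. Cancellation rates other than 20%, and unequal rates, are my assumptions.

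**Formulas** (pooled variance under the null, p̄ the mean of p1 and p2):

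n = [1.960·√(2p̄(1−p̄)) + 0.842·√(p1(1−p1)+p2(1−p2))]² / (p2−p1)²

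power = Φ{ [(p2−p1)√n − 1.960·√(2p̄(1−p̄))] / √(p1(1−p1)+p2(1−p2)) }

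**Step 1: reproduce 376.** p̄ = 0.40, so √(2 × 0.40 × 0.60) = 0.6928 and √(0.2275 + 0.2475) = 0.6892. The formula gives n = 375.6, rounded up to 376, with power 80.0%. The base figure is correct.

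**Step 2: the inflation.**
- 376 × 1.2 = 451.2, which explains 450.
- 376/0.8 = 470 per arm (940 in total), which is what 20% loss requires.
- 450 × 0.8 = 360, which is 16 short of 376.
- 1 − 376/450 = 16.4%, the largest loss that 450 can absorb.

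**Step 3: power if the 20% are excluded.** With n = 360, Φ{(0.10 × √360 − 1.960 × 0.6928)/0.6892} = Φ(0.783) = 78.3%. Exact binomial enumeration of the chi-square test gives 78.8%.

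**Step 4: power if cancelled women stay in the ITT analysis as non-events.** Take 35% and 45% as per-transfer rates and assume 20% cancelled in each arm. The rates become 0.8 × 35% = 28% and 0.8 × 45% = 36%, a difference of 8 points. Here p̄ = 0.32 and the two square roots are 0.6597 and 0.6573. With n = 450, Φ{(0.08 × √450 − 1.960 × 0.6597)/0.6573} = Φ(0.615) = 73.1% (exact: 73.1%). Reaching 80% would take 533 per arm, and 470 gives only 74.9%, so correcting Step 2 does not resolve this part.

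**Step 5: how far Step 4 depends on its assumptions** (450 per arm, two-sided 5%):

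| Reading | Control v letrozole, ITT | Power |
|---|---|---|
| Rates already per woman randomised | 35% v 45% | 86.6% |
| Per transfer, 10% cancelled in both | 31.5% v 40.5% | 80.4% |
| Per transfer, 20% in both | 28% v 36% | 73.1% |
| Per transfer, 30% in both | 24.5% v 31.5% | 64.8% |
| Per transfer, 20% control, 18% letrozole | 28% v 36.9% | 81.5% |
| Per transfer, 20% control, 15% letrozole | 28% v 38.25% | 90.6% |
| Per transfer, 20% control, 25% letrozole | 28% v 33.75% | 46.3% |

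Each ITT rate is the per-transfer rate times (1 − cancellation), for example 0.82 × 45% = 36.9%.

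**The case against.** The strongest reply is that the only error that can be shown without interpretation is small. It is 16 women per arm and under 2 percentage points of power, which alone would not overturn the adequacy claim. That stands.

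A reader might infer that 450 per arm fails to give 80% power on any reading, or that the trial's true power is 73%. The documents support neither. The 73% needs three things together:

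- **Per-transfer rates.** Allowing for cancelled transfers suggests this, since per-woman rates would already include them. But the article speaks of the proportion of women and never states the unit.
- **The whole 20% being cancellations.** Cancellation is given only as an example of dropout; its share is not stated.
- **Equal cancellation in both arms.** Freeze-all depends partly on estradiol, which letrozole is expected to lower, so cancellation could be less frequent in that arm. Two points less is enough to bring power above 80%.

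Equal 10% cancellation, 20% v 18%, and per-woman rates all give 80% or more.

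Two further replies have some weight. With 890 women recruited when the article was prepared, restated power changes no data, and the planned confidence intervals will show the precision of a null result directly. Also, the analysis section judges superiority by a 99% interval, so figures at two-sided 5% do not describe that criterion. The latter is a separate matter, but it is a reason to label the level beside any restated power.

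None of this removes the mismatch. If cancellation does differ by arm, excluding those women would break the randomised comparison, so the denominator matters more.

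**Conclusion.** The point holds in a limited form and should be fixed.

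- **Certain, on the article's own inputs.** The inflation is wrong. At 20% loss, 450 leaves 360 per arm against 376 required, and power is about 78% instead of 80%. The tolerated loss is 16.4%.
- **Certain, as an inconsistency.** Cancelled transfers are sized as losses, while the ITT analysis of a fresh-transfer outcome keeps those women as non-events. Inflation cannot repair that dilution.
- **Conditional.** The size of the ITT effect is not determined by the document. About 73% applies to per-transfer rates with 20% cancelled in both arms; the table in the working shows how widely power moves around it, in both directions.

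The Discussion's adequacy statement is therefore not established as it stands. It is not shown to be false either, because that depends on a unit and on cancellation rates that the article does not fix.

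**What to change.** No added enrolment is needed.

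1. Correct the inflation to 376/0.8 = 470, or keep 450 and state that it tolerates 16% loss and gives about 78% power at 20% loss.
2. State whether 35% and 45% are per woman randomised or per fresh transfer. Only the sponsor can say which was meant.
3. Fix the primary ITT denominator as all women randomised, with a cancelled fresh transfer counted as no event. Do this before outcome data are analysed.
4. Report ITT power for 450 per arm over a range of cancellation rates, including unequal arms. Label 73% as the scenario with per-transfer rates and 20% cancelled in each arm, at two-sided 5%.
5. Qualify the Discussion's statement on sample size to match.

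The cost is a few sentences and a small table. The downside is that the stated power becomes slightly less favourable.
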